**Materials and Methods:**

96 infertile women with PCOS, aged 18-40 yr, will participate in this randomized, placebo-controlled clinical trial. Based on treatment conditions and body mass index, the participants will be randomly divided into 4 equal groups using a randomized block design. They will receive a DASH or standard diet containing 52% carbohydrate, 18% protein, and 30% total fat, with the same prescribed sodium, plus 500 mg twice daily curcumin or placebo for 12 wk. The mRNA expression of *IL-1
α

*, *5
α

* reductase, and androgenic and glycemic profiles will be measured at baseline and at the end of the study.

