## 2. Materials and Methods

### Trial design and study setting

This randomized, placebo-controlled clinical trial will be conducted on PCOS women candidates for in vitro fertilization (IVF), using a convenience sampling method. Participants in a 2
×
2 factorial design will be randomly divided into 4 parallel treatment groups using block randomization: (1) curcumin supplement + DASH diet (2) curcumin supplement + standard diet (3) placebo + DASH diet, and (4) placebo + standard diet. The follow-up duration will be 12 wk. The study will be conducted at the Yazd Reproductive Sciences Institute, Shahid Sadoughi University of Medical Sciences, Yazd, Iran. An overview of the study is presented in figure 1.

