### Outcomes

The primary outcomes included gene expressions of IL-1α and 5α-reductase. The secondary outcomes consist serum levels of biochemical parameters comprising fasting blood sugar, fasting insulin, homeostasis model assessment of insulin resistance and quantitative insulin sensitivity check index, as well as serum androgen concentrations (testosterone, 5α-dihydrotestosterone) and anthropometric indices (height, weight, BMI, hip circumstance, waist circumstance, waist-hip ratio, waist-height ratio), body composition (muscle mass, fat mass, fat-free mass, and other factors such as trunk fat mass), physical activity, and dietary intake (energy and nutrient intake).

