### Sample size

The sample size of 24 in each group was determined according to α = 0.05, the power of 80%, dropout rate of 20%, and considering a minimal clinically important difference of 0.969 and an effect size of 1, based on Heshmati et al. study (21) using the following formula: 

$$n=\frac{{\left(Z_{1-\alpha /2}+Z_{1-\beta }\right)}^{2}\left(S_{1}^{2}+S_{2}^{2}\right)}{{\left(\mu_{1}-\mu_{2}\right)}^{2}}$$

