### Statistical methods

The values of quantitative variables will be presented as the mean 
±
 standard deviation, and qualitative variables will be expressed as numbers and percentages. The normality of data will be examined by the Kolmogorov-Smirnov test.

The frequency among study groups will be compared using the Chi-square test. Independent sample *t* test and 2-way ANOVA will be applied to estimate the mean of quantitative variable changes and interactions between study groups; Bonferroni correction will be considered for multiple comparisons; and analysis of covariance (ANCOVA) will be used to compare the differences in the mean of quantitative data between the studied groups, while taking into account the influence of possible confounding variables. Before statistical analysis, all data will be checked for accuracy and completeness. All statistical analysis will be conducted using SPSS 22 (SPSS, Inc, Chicago, IL, USA). A p-value 
<
 0.05 will be defined as a statistically significant level.

The “intention-to-treat" and “per protocol analysis" approaches will be performed for data analysis. The “intention-to-treat" analysis considers all participants in their main randomized groups, regardless of whether they follow the prescribed intervention according to the protocol or not, and also ignores non-compliance and withdrawal. Per protocol analysis, which accurately reflects what has been done, will be conducted based on actual adherence to the interventions.

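### Holm's step-down would be a cheap improvement on the Bonferroni correction named in the plan: same family-wise guarantee, never less power, with a gain that depends on the family and on how many effects are real

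*Protocol article*

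**What the plan says.** All of this is in the protocol article.

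- **Statistical methods** gives the multiplicity rule in one clause: "Bonferroni correction will be considered for multiple comparisons". The clause follows the sentence on group comparisons, where the independent-sample t "test and 2-way ANOVA will be applied to estimate the mean of quantitative variable changes and interactions between study groups". The threshold is given as p below "0.05 will be defined as a statistically significant level". The number of tests, the family and the split of alpha are not given.
- **Outcomes** names two primary endpoints: "The primary outcomes included gene expressions of IL-1α and 5α-reductase".
- **Trial design and study setting** describes a 2 × 2 "factorial design will be randomly divided into 4 parallel treatment groups using block randomization". Four arms allow six pairwise comparisons, or two main effects and an interaction.
- **Sample size** reads "The sample size of 24 in each group was determined according to α = 0.05, the power of 80%, dropout rate of 20" per cent, "considering a minimal clinically important difference of 0.969 and an effect size of 1". No multiplicity adjustment is mentioned there.

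**The concern.** Single-step Bonferroni compares every p-value in a family of m tests with 0.05/m. Holm's step-down orders the p-values and compares the smallest with 0.05/m, the next with 0.05/(m − 1), and so on, stopping at the first failure. Its first step is Bonferroni's threshold and every later threshold is larger. It therefore rejects whatever Bonferroni rejects and sometimes more. Like Bonferroni, it holds the family-wise error at 0.05 under any dependence between the tests.

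A trial with about 19 completers per arm, two primary genes and four arms has little power to spare. If several effects are real, Bonferroni can miss some that Holm would declare at the same family-wise guarantee. The Conclusion of the abstract anticipates reductions in both genes, so that situation is not far-fetched here.

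**Working it through.** **Inputs from the article:** 24 per group, 20% dropout, alpha 0.05 (two-sided, from the quantile in the printed formula), effect size 1, two primary genes, four arms. Completers per arm: 24 × 0.8 = 19.2, taken as 19.

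**Assumed, because the article does not give them:** the family (two genes on one two-arm contrast, two genes on a factorial main effect, or six arm pairs), the number of real effects, and the correlation between genes (0.3 unless stated).

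**The plan's own sample size.** The printed formula at effect size 1 is n = 2 × (1.960 + 0.842)² / 1² = 15.7, so 16 per group, and 16/0.8 = 20 after dropout. The stated 24 is larger, so the plan is not short of its own formula. With alpha split over two tests (0.025 each) the formula gives 19.01, and 19.01/0.8 = 23.8, so 24.

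**Two genes, one two-arm contrast, 19 v 19, both effects 1 SD.** Let p be the t-test power at 0.025 and q the power at 0.05: p = 0.768, q = 0.851. For independent tests:

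- Bonferroni: p = 76.8% per gene; p² = 59.0% for both.
- Holm per gene: p + p(q − p) = 0.768 + 0.768 × 0.083 = 83.2%.
- Holm for both: p² + 2p(q − p) = 0.590 + 0.127 = 71.7%.

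With correlation 0.3 (40,000 simulations), the per-gene figures are 76.8% v 82.6% and the figures for both genes 61.8% v 73.4%. The gains are 5.8 and 11.6 points. By the protocol's normal approximation with independent tests they are 5.5 (80.0% to 85.5%) and 11.1 (64.0% to 75.1%).

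**Other settings, 19 completers per arm:**

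| Family and truth | Bonferroni | Holm | Gain (points) |
|---|---|---|---|
| Two genes, only one responds: power for that gene | 76.6% | 76.8% | 0.2 |
| Two genes, both respond: power for at least one | 91.8% | 91.8% | 0 |
| Factorial main effect, 38 v 38, both genes 1 SD: per gene | 97.9% | 99.0% | about 1 |
| The same: both genes | about 96% | about 98% | about 2 |
| Six arm pairs, each factor adds 1 SD: each 1-SD pair | 64–65% | 74–75% | about 10 |
| Six arm pairs, one factor works (normal approximation): each 1-SD pair | 67% | 72% | 5 |
| Six arm pairs, one arm differs (normal approximation): each 1-SD pair | 67% | 70% | 3 |

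If each factor adds only 0.5 SD, the gain over the six pairs is about 0.6 to 2 points. If the factorial main effect is 0.5 SD rather than 1 SD, the per-gene gain is 5.3 points (46.1% to 51.4%).

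**False positives.** With all nulls true, the two procedures have the same family-wise error. With one gene real and one null, the null gene is rejected 2.5% of the time under Bonferroni and 4.4% under Holm. With six pairs and both factors adding 1 SD, the one null pair is rejected 0.8% v 2.5%. All stay below 5%.

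**The case against.** The strongest case against is that nothing here is wrong. Bonferroni is valid and conventional, the article says only that it will be considered, and it does not tie the correction to the two genes or to any count of tests. Defining the family is commonly left to an analysis plan, which is not shown. Bonferroni also has simple matching simultaneous intervals, which Holm lacks. Over two tests at 19 per arm it gives 80.0% power per test by the protocol's own approximation (76.8% by the t test), essentially the target.

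All of that stands, and it limits the point to an optional gain in efficiency. It does not remove the point: Bonferroni is the only method named, and for testing there is no setting in which it has more power than Holm.

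Three stronger readings are tempting, and the documents do not support them.

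- *The trial forfeits 6 to 11 points of power.* That range needs a two-gene family on one contrast with both genes responding by 1 SD, and it mixes per-gene power with power for both genes. Other settings give close to nothing.
- *Bonferroni buys no added protection.* The guarantee is the same, but when other effects are real Bonferroni rejects a true null less often (2.5% v 4.4%).
- *The 24 per group already allows for a two-test Bonferroni split.* The arithmetic matches, but the article states alpha 0.05 and mentions no split.

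**Conclusion.** A cheap improvement, not a correction of an error. The dominance in testing power is a mathematical property of the two procedures and needs no assumption about this trial. The size of the gain does. At 19 completers per arm it runs from near zero (one gene responding, or at least one gene to be shown), through 1 to 2 points (1-SD factorial main effects) and 3 to 5 points (one arm or one factor working, six pairs), to about 6 points per gene, 11 to 12 for both genes, and about 10 per 1-SD arm pair when most effects are real. These figures rest on the plan's effect size of 1, its 20% dropout, and assumed families and correlations. The importance is low: the trial stays valid if nothing is changed.

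**What to change.** Replace the Bonferroni clause, before unblinding, with wording such as:

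> Within each family of primary comparisons (the two genes; and, where arms are compared pairwise, the six arm pairs), p-values will be adjusted by Holm's step-down procedure at a family-wise level of 0.05. Bonferroni-adjusted confidence intervals will be shown beside them.

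This also settles what the families are. The 0.05 guarantee then applies within each family, not across families.

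The cost is one sentence, with no change to sample size, data collection or software: p-values from SPSS 22 can be ordered and adjusted by hand. There are two small downsides. A Bonferroni interval may occasionally include zero where Holm rejects, so the text should say that the adjusted p-value decides. A true null is also rejected somewhat more often than under Bonferroni when other effects are real, still within 0.05. If matching simultaneous intervals matter more to the investigators than the extra power, keeping Bonferroni is defensible.

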**Figure 1 F1:**
[figure not shown]
Overall overview of the study.

### Participants and public involvement

Participants or the public will not participate in the setting, execution, measuring outcome, or dissemination plans of our study. The study results will be provided to patients upon request. Research findings will be reported in scientific journals.

### Ethical considerations

This study will be conducted following the Declaration of Helsinki. This trial was approved on September 2020 by the Medical Ethics Committee of Shahid Sadoughi University of Medical Sciences, Yazd, Iran, (Code: IR.SSU.SPH.REC.1399.145).

All goals, working methods, and possible side effects of the interventions will be explained to all the participants before starting and entering the study by the main researcher, and an informed consent form will be obtained from the participants.

Participants will be assured that all their information will be kept confidential. The contact information of one of the researchers will be provided to the participants for 24-hr contact in case of any complications or problems. The study will have no financial burden on the participants.

### Monitoring

Data monitoring and safety program are considered for this study. Project managers ([name]) and a research advisor ([name]) will supervise and monitor the research process to ensure protocol compliance and data quality. Any withdrawals, lost to follow-up and adverse events will be assessed and reported. An independent trial Data Monitoring Committee will review the collected data and evaluate clinical trials for scientific validity, safety, and integrity.

### Study strengths and limitations

This will be the first study to investigate the effects of the DASH diet or curcumin supplementation on *IL-1
α

* gene expression in human. This study will be the first clinical trial that investigates the co-administration of the DASH diet and curcumin supplementation in patients with PCOS. The frequency of PCOS women with BMI: 18.5-25 is probably low, which could increase study time and lead to bias in results.

##  Availability of data and materials

The datasets analyzed during the current study will be available from the corresponding author upon reasonable request.
